# Effects of aerobic interval training on glucose tolerance in children and adolescents with cystic fibrosis: a randomized trial protocol

**DOI:** 10.1186/s13063-019-3803-8

**Published:** 2019-12-26

**Keywords:** Cystic fibrosis, Glucose tolerance, Aerobic exercise, Exercise, Respiratory function tests

## Abstract

**Background:**

Individuals with cystic fibrosis (CF) may develop CF-related diabetes (CFDR). This comorbidity is related to a poorer quality of life, microvascular complications, a decline in lung function, and an increase in exacerbations, as well as delayed growth and puberty. Evidence exists that physical exercise contributes to glycemic control in individuals with non-CF-related diabetes. This exercise is usually continuous with moderate intensity and long duration, which can cause muscle dyspnea and fatigue in CF individuals. Aerobic interval training (AIT) emerges as a safe and effective alternative for treating these individuals. The objective of this study is to evaluate the effects of AIT on glucose tolerance in children and adolescents with CF.

**Methods:**

This study will be a two-arm, prospectively registered, randomized controlled trial with blind assessors and twenty 6- to 18-year-old individuals with cystic fibrosis (CF) from two different Brazilian states. People with CF will be randomly allocated to either the experimental or control group using block randomization, stratified by puberty stage,. Participants from both groups will receive an educational intervention and will be asked to continue their usual daily treatment for the full duration of the study. Those in the experimental group will perform AIT on a cycle ergometer at home three times a week, for 8 consecutive weeks. The sample characterization will include an assessment of puberty stage, socioeconomic status, dyspnea, and anthropometry. The primary outcome will be the change in glucose tolerance, while the secondary outcomes will include lung function, exercise tolerance, respiratory muscle strength, quality of life, and CF exacerbations. All outcomes will be assessed at baseline, week 9, and week 17.

**Discussion:**

This is the first study to evaluate the effects of AIT on glucose tolerance in children and adolescents with CF. This study will serve as a basis for guiding clinical practice and decision-making in treating glucose intolerance and CF-related diabetes (CFRD) in children and adolescents with CF.

**Trial registration:**

ClinicalTrials.gov Protocol Registration System: NCT03653949. Registered on August 31, 2018.

## Background

Cystic fibrosis (CF) is the most common autosomal recessive, multisystemic, hereditary disease in Caucasians [1]. Due to technological advances, precise knowledge of CF pathophysiology has contributed to the discovery of new treatment approaches. These approaches have increased the life expectancy for individuals with CF [2], which in turn has led to late complications, such as bone disease [3], liver disease [4], depression and anxiety [5], and CF-related diabetes (CFRD) [6].

CFRD is the most common comorbidity in CF [7]. Its prevalence increases with age, ranging from 2% in children to 50% in adults age 30 years or older [6]. The mortality rate is 3.6 times higher in individuals who develop CFRD compared to those who do not [8]. In addition, CFRD is related to a poorer quality of life, microvascular complications, a decline in lung function, an increase in exacerbations, delayed growth, and problems with the development of puberty [9–11].

CFRD is preceded by a long phase of glucose intolerance and periods of postprandial hyperglycemia [12, 13]. It has distinct characteristics that include aspects of type 1 (T1DM) and type 2 diabetes mellitus (T2DM). Its pathophysiology is complex and includes a loss of pancreatic islet cells, which causes insulin and glucagon deficiency, fluctuating insulin resistance, intestinal abnormalities, and liver disease [7, 10].

Physical exercise has been incorporated as a recommended routine for individuals with CF [14]. Evidence exists that exercise decreases the risk of hospitalization [15]; increases the quality of life [16]; increases functional capacity and peak VO_2_ [17]; decreases general and physical fatigue [18]; increases lung function; facilitates airway clearance techniques; improves posture; and, finally, increases muscle strength, flexibility [19], and bone mineral density [19, 20]. The only study known to evaluate the effect of exercise in adults with CFRD reported an improvement in glycemic control [21].

Regarding individuals with glucose abnormalities or non-CF-related diabetes, physical exercise helps in managing blood glucose levels [22–24] and glycated hemoglobin [25]. It also improves the quality of life [22, 26] and increases the VO_2max_ [22] and pulmonary and immune function [24], as well as reducing the risk of cardiovascular disease [22, 24] and mortality [22].

Most physical exercise programs use continuous exercises of moderate intensity and long duration. This intervention increases the treatment time for individuals with CF and can cause unpleasant symptoms such as dyspnea and muscle fatigue [27, 28]. Aerobic interval training (AIT) emerges as a safe and effective alternative for treating individuals with CF [28, 29] because it produces a lower risk of airflow limitation [29], less systemic inflammation [30], less dyspnea, and greater peripheral oxygen saturation [27]. Until now, no studies have evaluated the effect of IT on glycemic control in children and adolescents with CF.

Therefore, this study aims to evaluate the effects of AIT in children and adolescents with CF for the outcomes of glucose tolerance, lung function, exercise tolerance, respiratory muscle strength, quality of life, and CF exacerbations. Our hypothesis is that AIT will improve all the outcomes.

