### Secondary outcomes

#### Lung function

Spirometry will be conducted using a KoKo DigiDoser spirometer (Longmonth, USA), as per the recommendations of the American Thoracic Society (ATS) and the European Respiratory Society (ERS) [43]. Manual calibration of the equipment will be conducted during the examination, following the instructions of the manufacturer and using a 3-L syringe (Vitalograph, Buckingham, England). A disposable mouthpiece and a bactericidal filter (MicroGard 36-MGF1100) will be attached to the apparatus. These parts will be replaced and discarded after each participant use.

A mouthpiece and nasal clip will be used to avoid leaks, and the individual will be instructed on their participation in the examination. The forced vital capacity (FVC), forced expiratory volume in the first second (FEV_1_), Tiffeneau index (FEV_1_/FVC), and forced expiratory flow between 25 and 75% of vital capacity (FEF 25–75) will be recorded in absolute values, as well as in percentages relative to gender, age and height. Up to three acceptable and two reproducible tests can be performed, and the highest value curve is recorded [44]. The values obtained in this study will be compared to the reference values proposed by Mallozi [45].

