#### Quality of life

The Cystic Fibrosis Questionnaire on Quality of Life, which was translated and validated into Portuguese in 2006, will be used for the quality-of-life evaluation. Four versions of the questionnaire exist, and these are adapted to different age groups: 6 to 11 years old (35 questions), 12 and 13 years old (35 questions), 14 years old or older (50 questions), and parents of children between 6 and 11 years old (44 questions). For children between 6 and 11 years old, the questionnaire will be supplemented with special cards for the child’s responses. The questionnaire addresses the following domains: physical health, body image, digestion, respiration, emotional state, social abilities, nutrition, treatment, vitality, health, social role, and weight. The scores for each domain range from 0 to 100, with a good quality-of-life scoring at or above 50 [53].

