### Statistical analysis

Intention-to-treat analysis will be employed to prevent overestimation of intervention efficacy. The numerical data will be presented in averages, while the categorical data will be presented in a frequency distribution. Once data collection is complete, the data distribution normality will be verified by the Shapiro-Wilk test.

Fisher’s Exact Test will be used for intragroup analysis of categorical data, while the two-way mixed-design analysis of variance (ANOVA) test (a repetition factor and a group factor), followed by the Bonferroni post hoc test, will be applied to the numerical data. The effect size (ES) will be analyzed using Cohen’s *f*. If data are non-parametric, the Friedman test with Dunn’s post hoc test will be used for intragroup analysis. The ES will be analyzed using Kendall’s *w*. The Mann-Whitney test will be applied for intergroup analysis, and the ES will be analyzed using Cohen’s *r*. Each ES will interpreted on the basis of Cohen as follows: small (0.21–0.49), medium (0.50–0.79), or large (≥0.80) [54].

All the analyses will consider a confidence interval of 95% (CI95%) and a statistical significance of *P* < 0.05. The Statistical Package for Social Science (SPSS) 20.0 (IBM Corp., Armonk, United States) will be used to analyze the data.

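### A blanket P < 0.05 rule gives about 20 secondary variables a full-level test each, with nothing controlling error across them

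*Protocol article*

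**What the plan says.** The protocol article ranks its outcomes. The Methods part of the Abstract says: "The primary outcome will be the change in glucose tolerance, while the secondary outcomes will include lung function, exercise tolerance", and then lists respiratory muscle strength, quality of life and exacerbations. The Background nevertheless attaches an efficacy hypothesis to every one of them: "Our hypothesis is that AIT will improve all the outcomes".

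The Statistical analysis section sets one significance rule for primary and secondary outcomes alike: "All the analyses will consider a confidence interval of 95% (CI95%) and a statistical significance of *P* < 0.05". Numerical variables go into a "two-way mixed-design analysis of variance (ANOVA) test (a repetition factor and a group factor"), and the only multiplicity correction is the step "followed by the Bonferroni post hoc test, will be applied to the numerical data".

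Several secondary outcomes consist of more than one variable. Spirometry yields four indices that "will be recorded in absolute values, as well as in percentages relative to gender, age and height". The quality-of-life questionnaire has 12 domains, each scored separately: "physical health, body image, digestion, respiration, emotional state, social abilities, nutrition, treatment, vitality, health, social role, and weight". The article names no lead variable for spirometry, respiratory pressures or quality of life. It does not make any secondary test conditional on the primary result, and it does not call the secondary outcomes exploratory or supportive.

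**The concern.** The Background and the Statistical analysis section together give each secondary variable a hypothesis of benefit and its own test at the full 0.05 level. Bonferroni comparisons after an ANOVA limit error among the visits or cells of one variable; they do nothing about the number of variables. In a trial of 10 children per arm, one spirometry index, one pressure or one questionnaire domain could reach P < 0.05 by chance. By the stated rule it would be reported as a significant effect with the same standing as the glucose result. What is at stake is how much weight such a finding may carry, above all if the primary outcome is null.

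**Working it through.** **The plan's own figure.** The protocol states no error rate across outcomes and no number of tests. Its one related figure is the sample size of 20 (Sample size calculation: 80% power, α 0.05, effect size 0.30). Taking 0.30 as Cohen's f, with 2 groups, m = 3 visits and an assumed between-visit correlation ρ = 0.5, the group-by-time interaction has noncentrality λ = f²·N·m/(1 − ρ) = 0.09 × 20 × 3/0.5 = 10.8 on 2 and 36 degrees of freedom. Power is 0.812, so N = 20 reproduces. The same interaction test is used below.

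**Count of secondary variables.**
- Lung function: FVC, FEV1, FEV1/FVC, FEF 25–75 = 4 (counted once, although absolute and percentage values are both recorded)
- Exercise tolerance: step count = 1
- Respiratory muscle strength: MIP, MEP = 2
- Quality of life: 12 domains
- CF exacerbations: 1
- Total: 4 + 1 + 2 + 12 + 1 = 20

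**Under independence, with no true effect.**
- Expected number of false positives: 20 × 0.05 = 1.
- At least one significant result in either direction: 1 − 0.95²⁰ = 64.2%.
- At least one significant result favouring training at week 9: each test contributes 0.05 × 1/2 = 0.025, so 1 − 0.975²⁰ = 39.7%.
- At least one favouring training at week 9 or week 17: under the null the two changes from baseline have correlation 0.5, so at least one is favourable with probability 2/3. Each test contributes 0.05 × 2/3 = 0.0333, so 1 − 0.9667²⁰ = 49%.

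**With correlated variables.** Null trials were simulated: 10 per arm, 3 visits, between-visit correlation 0.5, equal correlation between variables, interaction F test at 0.05. Ranges are across repeated runs.

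| Correlation between variables | Any significant, either direction | Significant, favouring training at week 9 or 17 |
|---|---|---|
| 0 | 64–66% | 50–51% |
| 0.3 | 54–57% | 39–41% |
| 0.5 | 43–44% | 31–32% |
| 0.7 | 30–31% | 21–22% |

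**Sensitivity to the count.**
- One variable per named secondary outcome (5 tests): 1 − 0.95⁵ = 22.6% under independence. Simulated values run from about 13% (correlation 0.8) to 24% (correlation 0), either direction.
- 9 and 16 independent tests: 37% and 56%, either direction.
- Exacerbation is categorical but was simulated as continuous. Dropping it gives 1 − 0.95¹⁹ = 62.3%, so this matters little.
- Not every child answers all 12 domains, because the questionnaire versions differ by age. Fewer children per domain does not lower the 5% error rate of each test, but fewer domains tested would lower the count.

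**The case against.** The strongest reply is that multiplicity among secondary outcomes is commonly left to a statistical analysis plan, that none is shown, and that unadjusted secondary outcomes beneath a named primary are common in small trials. It is right that the mere absence of an adjustment is no fault here, and that a directional scientific hypothesis is not an error in itself. What remains is stated text: the Statistical analysis section positively applies P < 0.05 to all analyses, so a later plan treating secondary outcomes as exploratory would have to override that sentence.

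It is also fair that the count of 20 is derived. The article does not say that each spirometry index or domain will be tested separately, so the percentages are conditional on that. Adding the step-test saturation, heart rate and Borg readings as endpoints would be speculative, and they are left out.

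Four stronger readings are tempting and are not supported:
- *That there is no hierarchy or adjustment at all.* One primary outcome is named, the sample size rests on a glucose variable, and Bonferroni is specified within each ANOVA. The gap is only among and across the secondary variables.
- *That one significant domain would confirm the stated hypothesis.* The Background hypothesises improvement on all outcomes jointly. A single significant result does not confirm that, and no passage says it would.
- *That a stray secondary result is set up to guide practice.* The Discussion ties its practice claim to glucose intolerance and CFRD, and makes its treatment claim conditional on improved glucose tolerance.
- *That the primary test is compromised.* Secondary tests do not change its error rate.

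**Conclusion.** The point holds as a matter of what the trial may conclude from its secondary outcomes. With about 20 variables each tested at 0.05 and no true effect, at least one significant interaction in either direction has a chance of about 64% under independence and about 31–57% at correlations of 0.3–0.7. For a result favouring training at week 9 or 17, the figures are about 50% and about 22–41%.

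A reader might infer that a chance benefit is likely. That goes too far: the 64% includes results favouring control, and the favourable figure reaches about one half only under independence, which is implausible for spirometry indices, pressures and questionnaire domains measured in the same children. The risk is substantial, and it persists at a smaller size (about 13–24%, either direction) with only one test per named secondary outcome.

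These figures assume that every listed variable is tested, that tests are two-sided, that the correlation between visits is 0.5 with sphericity, and that variables are equally correlated. The protocol gives none of these. The change is worth making, but the primary comparison does not depend on it.

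**What to change.** In the Statistical analysis section, restrict the P < 0.05 efficacy decision to the primary outcome. Add that secondary outcomes are exploratory, are reported as between-group differences with 95% confidence intervals, and support no efficacy claim on the strength of their P values. In the Background, make the confirmatory hypothesis the primary outcome only; expected benefit on the other outcomes can stay as a scientific expectation.

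The cost is wording in two places. No extra data or participants are needed, and the sample size of 20 is untouched because it rests on the primary outcome. The downside is that an isolated significant secondary result can no longer be presented as confirmed benefit. The alternative, a Bonferroni correction across 20 variables, would test each at 0.05/20 = 0.0025 and hold the chance of any false positive to 1 − 0.9975²⁰ = 4.9% under independence, but at a threshold that leaves little power with 10 children per arm.

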## Methods

### Study design

This is a two-center, prospectively registered, two-arm, randomized controlled trial with concealed allocation, blinded measurers, intention-to-treat analysis, and 8 weeks of follow-up (Fig. 1). Children and adolescents with CF will be recruited from hospitals specialized in treating the disease in the Brazilian states of Rio Grande do Norte and Paraíba. The recruitment will take place between August 2018 and December 2020.

**Fig. 1 Fig1:**
[figure not shown]
Flow diagram of the planned protocol

### Ethical procedures

The study has obtained ethical approval from the Research Ethical Committee of Universidade Federal do Rio Grande do Norte (CAAE: 88024518.9.1001.5537) under registration number 2.683.882. The trial was prospectively registered at the ClinicalTrials.gov Protocol Registration System (NCT03653949). All participants and their parents will sign an informed consent form prior to participation. The study follows the SPIRIT (Standard Protocol Items: Recommendations for International Trials) 2013 checklist and the TIDieR (Template for Intervention Description and Replication) [31] (Fig. 2 and Additional file 1).

**Fig. 2 Fig2:**
[figure not shown]
Study design schedule in accordance with the standard protocol items: Recommendations for Interventional Trials (SPIRIT) checklist

### Inclusion criteria

The inclusion criteria include the following:
Diagnosis of cystic fibrosis, according to the Brazilian Guidelines for diagnosis and treatment of CFAge from 6 to 18 yearsBoth sexesNot pregnant, in the postpartum period, or lactating.

### Exclusion criteria

The exclusion criteria include the following:
Present inability to perform the protocol established by the studyHave exacerbation of the disease, with hospitalization required during the intervention period [32]

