### Sample size calculation

The sample size calculation was performed by GPower 3.1 software, with a power of 80% and an α of 0.05 being adopted. This procedure was based on the study by Beaudoin et al. (2017) [21], which presents a similar design regarding the same number of groups and the use of exercise as an intervention, although it was developed for adults with CF. In this study, the variable area under the glucose curve after the concurrent exercise program presented values of 34.47 ± 4.23 in the experimental group (EG) and 40.20 ± 11.96 in the control group (CG), with an effect size of 0.30. Based on these parameters, the sample size calculation was 20 participants, with 10 in each group.

The children and the adolescents who discontinue participation in the study will be invited to participate in the assessments 8 weeks after starting treatment, as well as 8 weeks after the end of the intervention. Thus, all individuals will be included in the intention-to-treat analysis.

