#### CF exacerbations

In order to evaluate CF exacerbations, which normally require an increase and/or modification of antibiotics, the following Fuchs criteria adapted by the European Consensus Group will be used [32]: change in volume and/or color of secretion; increases in coughing, fatigue or lethargy; anorexia or weight loss; decrease in lung function of 10% or more as observed on X-ray; and increased dyspnea. The individual must present at least two of these criteria for an exacerbation to be confirmed.

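### An exclusion criterion is triggered by a hospitalised exacerbation after randomisation; read literally, it removes participants on a trial outcome and contradicts the intention-to-treat analysis

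*Protocol article*

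**What the plan says.** Four parts of the protocol article bear on this point.

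- **Exclusion criteria.** One of the two criteria is an "exacerbation of the disease, with hospitalization required during the intervention period". The Abstract gives the length of that period: training takes place "three times a week, for 8 consecutive weeks".
- **Analysis population.** Study design names intention-to-treat as a feature of the trial. Statistical analysis says "Intention-to-treat analysis will be employed to prevent overestimation of intervention efficacy". Sample size calculation says that those "who discontinue participation in the study will be invited to participate in the assessments 8 weeks after starting treatment", and again 8 weeks after the intervention ends. It concludes: "Thus, all individuals will be included in the intention-to-treat analysis".
- **Outcomes.** According to the Abstract, "the secondary outcomes will include lung function, exercise tolerance, respiratory muscle strength, quality of life, and CF exacerbations". The section on CF exacerbations gives the case definition: "The individual must present at least two of these criteria for an exacerbation to be confirmed". It cites the same reference as the exclusion criterion.
- **Hypothesis.** The Background expects training to improve every outcome, which includes exacerbations.

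**The concern.** An exclusion criterion normally describes a participant's status before randomisation. This one describes something that happens while the intervention is running, so it cannot be checked at screening and can act only on participants already randomised.

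The event is also a severe form of a secondary outcome. If training changes the risk of hospitalisation, in either direction, the criterion would remove different numbers and kinds of participants from the two arms. Those who remain would no longer be the groups that randomisation formed. The comparisons of glucose tolerance (the primary outcome), lung function and quality of life could then be biased, and the article gives no basis for predicting the direction. Hospitalised exacerbations during the 8 intervention weeks would also drop out of the efficacy comparison for the exacerbation outcome itself.

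**Working it through.** **Step 1: timing.** Under Intervention and Control group, the baseline assessment comes first and the educational session follows in week 1. Only the experimental group trains, so assignment precedes the 8 training weeks. An event during those weeks is therefore a post-randomisation event.

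**Step 2: the two rules side by side.** For a participant admitted with an exacerbation in, say, week 5:

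| Section | Consequence if read literally |
|---|---|
| Exclusion criteria | Excluded from the trial |
| Study design; Statistical analysis | Intention-to-treat applies |
| Sample size calculation | Everyone is in the analysis; those who discontinue are invited to both later assessments |

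The first row cannot hold together with the other two unless exclusion is meant as something less than removal, and the article does not say that it is.

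**Step 3: how likely the rule is to act.** The article gives no hospitalisation rate, so a range is assumed. With 20 participants and a common, independent risk q over 8 weeks, P(at least one removal) = 1 − (1 − q)^20, and the expected number of removals is 20q.

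| Assumed q | Expected removals | P(at least one) |
|---|---|---|
| 5% | 1 | 1 − 0.95^20 = 0.64 |
| 10% | 2 | 1 − 0.90^20 = 0.88 |
| 20% | 4 | 1 − 0.80^20 = 0.99 |

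Each removal is 1/10 = 10% of an arm, or 1/20 = 5% of the trial.

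**Step 4: reproducing the planned sample size.** Inputs from Sample size calculation: effect size 0.30, α = 0.05, power 80%, 20 participants in two groups. Three visits (m = 3) come from the Abstract, and the two-way mixed ANOVA from Statistical analysis. Not stated, and assumed here: the effect size is Cohen's f, the test is the group-by-time interaction, the correlation between visits is ρ = 0.5, and sphericity holds.

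- Noncentrality: λ = f²·N·m/(1 − ρ) = 0.09 × 20 × 3/0.5 = 10.8.
- Degrees of freedom: (2 − 1)(3 − 1) = 2 and (20 − 2)(3 − 1) = 36.
- Power = 0.812, and 20 is the smallest even N that reaches 80%. The stated figure reproduces.

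The result depends on ρ. At N = 20, power is 0.662 with ρ = 0.3 (80% would need 28) and 0.962 with ρ = 0.7 (14 would be enough). Of these three values, only ρ = 0.5 gives 20.

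**Step 5: the same model after removals** (ρ = 0.5, lost participants not replaced).

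| N analysed | λ | Power |
|---|---|---|
| 20 | 10.80 | 0.812 |
| 19 | 10.26 | 0.789 |
| 18 | 9.72 | 0.763 |
| 17 | 9.18 | 0.734 |
| 16 | 8.64 | 0.703 |

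The article states no allowance for losses, so the first removal already takes power below 80%. These figures count lost numbers only. They do not measure bias, which is the more serious consequence and cannot be sized from the article.

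**The case against.** The best defence is that removal from analysis is nowhere stated. The criterion might mean only that the participant's part in the trial ends, with Sample size calculation then governing follow-up and analysis. Intention-to-treat appears in three places, so the right principle is already written down. This reading is possible, and it is why the removal must be put conditionally: a reader might take it as settled that these participants are dropped, and the article does not go that far. But it does not state the benign reading either. The event is listed as an exclusion, while the follow-up provision speaks of those who discontinue, not of those whom the trial excludes. The conflict therefore stands.

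Other limits on the point also stand:

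- A reader might infer that hospitalised exacerbations would be zero in both arms throughout. The criterion covers only the 8 intervention weeks; events from then to week 17 are untouched. The outcome definition does not require hospitalisation, so milder exacerbations still count.
- A reader might infer that harm would be hidden. Patient safety provides for adverse-event monitoring in both arms. That does not return the events to the efficacy comparison, but it rules out saying that harm would go unseen.
- A reader might extend the point to the other criterion, inability to perform the protocol. That reads naturally as a screening rule, and study procedures such as the glucose tolerance test, spirometry and step test apply to both arms. The article does not support a charge of post-randomisation, one-sided exclusion there.
- The event is a subset of one secondary outcome, not the primary outcome.

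**Conclusion.** The point holds as a contradiction in the current text, not as missing detail. An exclusion criterion that can act only after randomisation, and on a severe form of a trial outcome, stands beside a promise to analyse everyone by intention-to-treat. If the criterion is followed literally, randomised participants are lost for a reason that training may influence.

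With 10 per arm, the rule would probably act at least once: the chance is 64% to 99% for an assumed risk of 5% to 20% over 8 weeks, independent and equal across participants. The fall in power from 0.81 to 0.79 with one loss, or to 0.70 with four, rests on the assumed ρ = 0.5 and the other assumptions that reproduce the planned sample size. The contradiction itself depends on none of these numbers.

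**What to change.** Reconcile Exclusion criteria with Sample size calculation:

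1. Limit the exclusion criteria to status before randomisation.
2. State that an exacerbation requiring hospitalisation after randomisation counts as an event for the exacerbation outcome.
3. State that the participant stays in the assigned arm for all analyses.
4. State that the week-9 and week-17 assessments are still attempted, as is already promised for those who discontinue.

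Whether training pauses or stops for such a participant is a clinical matter and is not addressed here.

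The cost is a wording amendment; the planned sample size stays at 20. The downside is that some outcomes will be measured in recently ill participants, which adds variability.
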